#### Sample Size

Sample size calculation was undertaken using procedures provided by the software program G*Power 3 [37]. As per our statistical consultant, the calculation was undertaken to determine adequate power in the determination of the potential effects of the intervention (aim 3), in which a repeated-measures ANOVA with a within-between interaction would be the statistical test used. The parameters for the power calculation included an effect size of 0.25 (standard medium effect size for ANOVA) [38], α of .01, and a power of 0.95. The sample size was further increased to account for a 30% attrition rate over the study duration, determined to be appropriate given a review of attrition rates in supportive oncology trials found a mean of 26% (95% CI 23%-28%) across 18 trials (ie, the original sample size was 36, total with added 30%, attrition is 52) [39].

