### Recruitment, Consent, and Randomization

Participant recruitment occurred at the cancer center in two ways. First, a member of the oncology clinical care team (oncologist, radiation oncologist, nurse, or administrative staff) briefly explained the study and asked patients if they were interested in hearing more about the study. If yes, a member of the study team was informed (in-person, email, or telephone) and contacted the patient. Second, a study poster placed at relevant locations within the cancer center contained the contact information (QR code, email, and telephone number) of the study team. The patients then contacted the team directly.

Interested individuals met with a member of the research team in person or communicated over email or telephone. Study details were provided, and eligibility was verified. If still interested and eligible, a secure link to an electronic consent form was emailed, followed immediately by the baseline questionnaire. Participants were randomly assigned to intervention plus usual care (experimental group, n=26) or usual care only (control group, n=26). Once initial consent was given, those in the experimental group reconsented. Participants in the control group were blinded to group assignment (Article 3.7A of Tri-Council Policy Statement 2) [44]. The randomization sequence was determined on R (R Core Team), a software program, using the randomized R package for clinical trials [45]. Diagram of study design, measurement points, and timeline is shown in Figure 5.

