### Data Collection

In both groups, follow-up e-questionnaires were completed every week for the first month and 2 weeks for the following 4 months, or until treatment was completed (if less than 5 months). Given the considerable variability in the duration of time patients may remain on OAAs, the study duration of 5 months was established as a long enough period in consultation with medical oncologists and pharmacists and was deemed appropriate for assessing the primary outcomes of feasibility and acceptability. Participants were monitored more closely during the first treatment cycle, as this period is critical for identifying potential toxicities and making necessary dosage adjustments. Furthermore, it is crucial to establish positive medication adherence behaviors early in the treatment process [46]. After 5 months or until OAA treatment was completed (if less than 5 months), participants completed the exit questionnaire, and a subset of participants in the experimental group (n=10) and control group (n=10) who had completed the study were invited to participate in a semistructured interview.

All e-questionnaires were completed on Qualtrics, a secure web-based electronic data capture system licensed through McGill University [47]. A data management plan between the university and the affiliated hospital was established for the study (Multimedia Appendix 1). Details of each measure and timepoint are provided in Table 1.

Baseline questionnaires completed by all participants included sociodemographic and medical characteristics, cancer information-seeking preferences, and OAA knowledge.

**Table 1 table1:** Study data collection.

Objective and measure			Instrument		Items, n		Time of collection				
						Baseline		Weekly for the first cycle	Every 2 weeks for cycles 2-5	Final questionnaire	Study completion

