### Data Analysis

Statistical analyses to be performed rely on Microsoft Excel, SPSS (version 25; IBM Corp) [65], and R (R Project for Statistical Computing) software [66]. For PDC, independent sample 1-tailed *t* tests will be performed to calculate the difference between 2 independent means of the experimental and control groups at one time point—study completion. Changes over time in MARS-5, MASES, and ESAS-r will be assessed using repeated-measures ANOVA. Between-group analyses will be conducted to examine how each group changed over time, and within-group analyses will be conducted to examine how participants changed over time.

The relationship between objective (PDC) and subjective (MARS-5) measures of medication adherence will be assessed using Spearman correlation coefficients. Oral chemotherapy knowledge at baseline and study exit will be compared using paired sample 1-tailed *t* tests.

Interviews were conducted individually, audio recorded, and transcribed verbatim by the first author, a doctoral candidate at the time with experience in qualitative research in oncology working on her dissertation. A reflexive journal was kept to document thoughts and feelings to recognize, acknowledge, and mitigate the influence of her role as a researcher and as someone with lived experience as an informal caretaker for a parent. Interview data were analyzed by the same author using thematic analysis as described by Braun and Clarke [67,68], beginning with several thorough readings of participant verbatim content to familiarize the researcher with the data and the identification of significant statements relating to the phenomenon under investigation [69]. Next, significant statements were placed into initial categories and organized into broader themes and subthemes. Themes and subthemes were reviewed, redefined, renamed, and explored as needed until no new themes emerged from the data.

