## Results

Data collection was completed as of December 2023 with a final sample of 41 (experimental group, n=23; control group, n=18), considering 11 dropouts after consent. Results are expected to be published in 2025 in a separate manuscript. Figure 6 presents the CONSORT flow chart for the study.

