### Conclusion

As remote consultations are still used for patients who are immunocompromised in the current period, the proposed intervention is still very relevant. Whether the COVID-19 pandemic may have acted as a confounding factor in this study remains unclear. In addition, since the study took place in a single setting, the next steps should include a multisite investigation to determine whether it is scalable and relevant across settings and geographical regions. The study sample is small, with 41 participants completing the study included in the final analysis for preliminary effects. Whereas the final sample is smaller than anticipated (41 vs 52), reliance on mixed methods provides complementary evidence. Dissemination activities related to the study results and its tested intervention include presentations at tumor boards, scientific publications, conference presentations, and diffusion through professional networks and webinars, as well as patient representative groups.

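### The preliminary-effects analysis is a repeated-measures ANOVA in the 41 completers (23 vs 18), not in the 26 vs 26 randomised, so arm-related dropout may bias it

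*Protocol article*

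**What the plan says.** All places are in the protocol article.

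- **Randomisation** (Recruitment, Consent, and Randomization): "Participants were randomly assigned to intervention plus usual care (experimental group, n=26) or usual care only (control group, n=26"). The Abstract places the baseline questionnaire before randomisation.
- **Analysis set** (Conclusion): the sample is described as small, "with 41 participants completing the study included in the final analysis for preliminary effects". Results gives a "final sample of 41 (experimental group, n=23; control group, n=18), considering 11 dropouts after consent".
- **Method** (Data Analysis): "Changes over time in MARS-5, MASES, and ESAS-r will be assessed using repeated-measures ANOVA". Sample Size says the same of the power calculation, for which "a repeated-measures ANOVA with a within-between interaction would be the statistical test used".
- **Follow-up** (Data Collection): questionnaires are weekly for the first month, then every two weeks for four months, "or until treatment was completed (if less than 5 months").
- **Expected completeness** (feasibility objectives, response rate): the target is that at least 70% of those who complete the study answer the outcome measures at all time points.
- **Baselines** (Table 1): MASES and ESAS-r are collected at baseline; MARS-5 is not.

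The article mentions no analysis of all randomised participants, no mixed model and no sensitivity analysis for aim 3.

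**The concern.** Randomisation makes the two groups of 26 comparable. It does not do so for the 23 and 18 who stayed to the end. Leaving the study happens after assignment and can depend on the arm and on how the patient is faring with adherence or symptoms. A contrast among completers can then show an effect that is not there, or hide one that is.

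The method adds a second layer of selection. In its standard form, repeated-measures ANOVA uses only people with a value at every occasion. Here some gaps are built in, because follow-up ends when treatment ends, and others are accepted through the 70% response objective. The patients left in the analysis would tend to be those with longer treatment and the most regular responses.

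At stake is the evidence on potential effects. The article states directional between-group hypotheses for aim 3, sizes the trial on that aim and proposes a multisite investigation as the next step.

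**Working it through.** **1. The plan's own sample size.** The inputs in Sample Size are "an effect size of 0.25 (standard medium effect size for ANOVA) [38], α of .01, and a power of 0.95". The number of occasions m and the within-person correlation rho are not given, so they are assumed here, with sphericity. For the within-between interaction with k = 2 arms:

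- lambda = f² × N × m / (1 − rho), df1 = (k − 1)(m − 1), df2 = (N − k)(m − 1).
- N = 36 is the required total at m = 6, rho = 0.5 (power 0.951). It is also the required total at m = 10, rho = 0.3 and at m = 3, rho = 0.7.
- 36 / (1 − 0.30) = 51.4, rounded up to 52. This agrees with the article: "the original sample size was 36, total with added 30%, attrition is 52".

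The figure is reproducible, but several settings give it, so the setting used cannot be recovered.

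**2. Dropout by arm.** The inputs are 26 and 26 randomised, and 23 and 18 in the final sample.

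- Experimental: 26 − 23 = 3; 3/26 = 11.5%.
- Control: 26 − 18 = 8; 8/26 = 30.8%.
- Check: 3 + 8 = 11, the stated number of dropouts. Overall 11/52 = 21.2%, below the 30% allowed for.
- Difference: 30.8% − 11.5% = 19.2 points before rounding (5/26). Wald 95% CI -2.3 to 40.8 points; Fisher exact p = 0.17.

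**3. Possible shift in the arm contrast.** Let d be the completer mean minus the dropout mean, in SD units, the same in both arms. In an arm with dropout proportion p, the completer mean exceeds the mean of all randomised by p × d. The completer contrast (experimental minus control) is therefore off by (3/26 − 8/26) × d = −0.192 d.

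| Assumed d (SD) | Size of shift (SD) |
|---|---|
| 0.2 | 0.04 |
| 0.5 | 0.10 |
| 1.0 | 0.19 |

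On a scale where higher is better, if dropouts are worse off the completer analysis understates the experimental arm; if they are better off it flatters it. The documents do not say which applies.

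**4. Completeness that the method requires.** The schedule gives about 4 + 8 = 12 follow-ups, or 13 occasions with baseline for MASES and ESAS-r. If exactly 70% of the 41 answered at every time point, 0.70 × 41 = 28.7, about 29, would have full data. This shows what the stated objective would permit; it is not a forecast.

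**5. Whether this is a power problem.** At f = 0.25, alpha = .01 and rho = 0.5 (assumed), 41 participants give power 0.977 with m = 6. With 29 participants, power is 0.871 at m = 6 but 0.991 at m = 12. The answer depends on a number of occasions that the article does not state.

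**The case against.** The strongest reply is that this is a pilot. Data Collection names feasibility and acceptability as the primary outcomes, aim 3 is meant to show trends, and the Conclusion openly reports the smaller final sample. That stands, and it lowers the severity. It does not make a completer contrast a comparison of the randomised groups.

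Other points on that side:

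- **The 3 versus 8 split is derived.** The flow diagram is not shown, and the 11 dropouts are described as occurring after consent, so some could in principle precede randomisation. The Abstract and the randomisation section both give 26 per arm as assigned, which makes the derivation the natural reading. The imbalance is not statistically significant, but bias does not depend on a significant imbalance.
- **Case deletion is not written down.** It follows from the named method in its standard form; the text does not describe how missing questionnaires are handled.
- **The shift in step 3 is hypothetical.** It concerns the mean contrast. It should not be set against the planned f of 0.25, which refers to a group-by-time interaction; a shift that is constant over time adds nothing to an interaction.

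A reader might infer that losses take the analysis below the 36 needed and leave it underpowered. The documents do not support that. The 41 exceed 36, attrition was below the allowance, the 70% is a minimum success criterion, and the result in step 5 changes with unstated inputs. A reader might also infer that PDC is restricted to completers. That rests only on the general sentence in the Conclusion; neither the PDC section nor Data Analysis says so.

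**Conclusion.** The point holds in a limited form. Followed as written, the plan compares 23 with 18 completers by a method that in its standard form needs every occasion, in a design where some occasions will be absent. The result is not a comparison of the groups as randomised, and it may be biased by dropout that was more frequent in the control arm (30.8% versus 11.5%).

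The plausible size is about 0.04 to 0.19 SD in the mean contrast. This rests on two assumptions: that dropouts differ from completers by 0.2 to 1 SD, and that the difference has the same direction and size in both arms. The dropout split itself rests on all 11 having left after randomisation.

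This should be fixed before effect estimates are used to plan a larger trial. It does not threaten the primary outcomes.

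**What to change.** For MASES, ESAS-r and MARS-5, replace repeated-measures ANOVA with a likelihood-based linear mixed model as follows:

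- **Population:** all randomised participants, in the arm assigned, with any available data. MARS-5 has no baseline, so it uses those with at least one follow-up; all 52 may not be reachable for that outcome.
- **Terms:** arm, time and arm-by-time, with the baseline score for MASES and ESAS-r. Report the between-arm difference with its confidence interval.
- **Covariance:** a parsimonious structure. An unstructured matrix for 13 occasions has 13 × 14 / 2 = 91 parameters, too many for at most 52 people.
- **End of treatment:** treat occasions after OAA treatment has ended as outside the adherence outcome, not as missing values.
- **PDC:** state the population, and compute it for all randomised participants with pharmacy consent and records.
- **Sensitivity analysis:** keep the 41-completer analysis, labelled as such.

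The cost is a change of wording and some extra modelling in SPSS or R, both already named; no new data are needed. The model relies on data being missing at random, which cannot be verified but is weaker than what the completer analysis needs. Data collection has closed, so the change should be dated and, if arm comparisons have already been run, reported as made afterwards.

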**Baseline information**											
	Sociodemographics	—^a^		12		✓		—	—	—	—
	Medical characteristics	—		7		✓		—	—	—	—
	Oral anticancer agent knowledge	—		9		✓		—	—	✓	—
	Cancer information-seeking preferences	Cancer information-seeking profiles		1		✓		—	—	✓	—

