The potential effects of the intervention (aim 3) will be assessed by comparing experimental and control groups over time, from baseline, every 2 weeks (depending on the outcome), and after the intervention in terms of the following outcomes: medication adherence SE, medication adherence (self-report and pharmacy records), and symptom distress.

Study feasibility objectives.

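### Knowledge is analysed only by a 1-tailed paired baseline-to-exit t test with no between-arm contrast, so a change in it cannot be attributed to the intervention

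*Protocol article*

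**What the plan says.** The Data Analysis section fixes one analysis for knowledge: "Oral chemotherapy knowledge at baseline and study exit will be compared using paired sample 1-tailed" t tests. It names no arm, no between-arm contrast and no alpha.

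The data for a randomised comparison appear to exist. Data Collection states: "Baseline questionnaires completed by all participants included sociodemographic and medical characteristics, cancer information-seeking preferences, and OAA knowledge". In Table 1 the row "Oral anticancer agent knowledge" is ticked at baseline and at the final questionnaire, with no restriction by arm. The Knowledge section does restrict the acceptability scale to the experimental group, so the article marks such limits when they apply.

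The longitudinal analysis covers other outcomes: "Changes over time in MARS-5, MASES, and ESAS-r will be assessed using repeated-measures ANOVA". Knowledge is not among them. Nor is it in the list of aim 3 outcomes, which are "medication adherence SE, medication adherence (self-report and pharmacy records), and symptom distress". Table 1 files it under baseline information.

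**The concern.** Knowledge lies close to what the intervention delivers. The videos and e-handouts are informational, and the Background gives knowledge a place in the route to self-efficacy. A reader will want to know whether the intervention raised it.

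A paired comparison cannot answer that. Control participants keep their contact with oncologist, pharmacist and nurse (end of Medication Reminders). Both arms gain up to five months of treatment experience, and both see the same items twice. A gain in both arms is plausible even if the intervention does nothing, and the paired test rejects for that shared gain just as it would for an intervention effect. The control arm is there to remove it, but the stated analysis does not use it for this purpose.

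**Working it through.** **Plan's own figure.** None is given for the knowledge test. The trial's sample size does not bear on this point.

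**Inputs from the article.** Final sample 41: 23 experimental, 18 control (Results). Paired, 1-tailed t test (Data Analysis).

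**Assumptions.** All 41 have both knowledge scores. The intervention effect is zero. Both arms gain d standard deviations of the change score, with d from 0.2 to 0.5. Alpha is .05, or .01; the latter is the only alpha in the article, given under Sample Size for another test.

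**Step 1: paired test under a shared gain.** The statistic is noncentral t with n − 1 degrees of freedom and noncentrality d√n. The probability of significance is P(T > t[1−α, n−1]).
- n = 23, d = 0.5: noncentrality 0.5 × √23 = 2.40.
- n = 41, d = 0.5: noncentrality 0.5 × √41 = 3.20.

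| Shared gain d | n = 23, α .05 | n = 41, α .05 | n = 23, α .01 | n = 41, α .01 |
|---|---|---|---|---|
| 0.2 | 24% | 35% | 8% | 14% |
| 0.3 | 40% | 60% | 17% | 32% |
| 0.5 | 75% | 93% | 47% | 78% |

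A simulation of 20,000 trials agrees for the 0.5 SD case. With a baseline-exit correlation of 0.5 and α .05, the paired test was significant in 75.4% (n = 23) and 93.7% (n = 41).

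**Step 2: does sidedness matter?** A two-sided paired test at .05 with n = 23 rejects in 15%, 28% and 63% for d = 0.2, 0.3 and 0.5. The missing contrast is the main fault; the tail is secondary.

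**Step 3: one paired test per arm.** With n = 18 at 1-tailed .05, the control arm is significant in 20.3%, 33.6% and 65.2%. The arms are independent, so the chance that only the experimental arm is significant is:
- d = 0.2: 0.237 × (1 − 0.203) = 19%
- d = 0.3: 0.401 × (1 − 0.336) = 27%
- d = 0.5: 0.751 × (1 − 0.652) = 26%

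That pattern looks like an effect when there is none.

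**Step 4: between-arm comparison.** The shared gain cancels, so the false-positive rate is the nominal one. In the simulation, two-sided baseline-adjusted ANCOVA at .05 rejected in 5.1%.

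For a true difference D in mean change (in SD of the change score), the noncentrality of the change-score t test is D × √(23 × 18 / 41) = 3.178 × D, with 39 degrees of freedom. Two-sided power at .05 is 34% for D = 0.5 and 70% for D = 0.8. Power of 80% needs about 0.90 SD, or about 1.12 SD at .01.

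The standard error of the difference is √(1/23 + 1/18) = 0.315 SD, so a 95% interval extends about 2.02 × 0.315 = 0.64 SD each way.

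**The case against.** The strongest reply is that the paired test answers its own question, whether knowledge changed, and answers it correctly. The rates in Step 1 are not false positives for that question. They mislead only if the change is taken as an intervention effect. This stands. A reader might infer that the trial will report a knowledge gain as an effect, but the article does not say so: knowledge is outside the hypothesis in Purpose of Study and outside the aim 3 list.

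The plural t tests may also mean one test per arm, which would at least display the control change. The text leaves this open. Step 3 shows why it would not be enough: two separate p values are not a comparison of arms.

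The rates depend on an assumed gain and an assumed alpha, and at 0.2 SD and .01 they are small. This also stands, and is why ranges are given.

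Two wider readings are tempting and unsupported:
- **The 1-tailed test of proportion of days covered shares the fault.** It does not. That is an "independent sample 1-tailed" t test between arms, and the article states a directional hypothesis for adherence.
- **The sentence "Between-group analyses will be conducted to examine how each group changed over time" abandons the arm-by-time contrast.** It is loosely worded, but Sample Size says a "repeated-measures ANOVA with a within-between interaction would be the statistical test used", and both the hypothesis and the aim 3 text compare the groups over time.

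**Conclusion.** The concern holds in a limited form. The only stated analysis of knowledge has no between-arm contrast, although the article indicates that both arms supply the data. Any change found, pooled or per arm, therefore cannot be attributed to the intervention. The size of the problem depends on the shared gain and alpha assumed in the working, neither of which the article supplies; across the ranges shown it runs from small to near-certain significance with no intervention effect. The 1-tailed choice has no stated hypothesis behind it for knowledge, but it adds little.

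Knowledge is an ancillary measure in a pilot whose primary outcomes are feasibility and acceptability, so this does not threaten the main conclusions. It is worth correcting because the better comparison needs no new data.

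**What to change.** Replace the paired test as the inferential analysis. Compare exit knowledge between arms by ANCOVA adjusted for baseline knowledge, two-sided, and report the adjusted difference with its confidence interval. Give within-arm change descriptively and say that it is not evidence of effect.

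Before scoring, reconcile the item count: the Knowledge section describes 7 items and Table 1 lists 9.

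The cost is a change of analysis wording. Because data collection has finished, the change should be dated and labelled as such. The price in precision is real: with 23 against 18, only a large difference would be detected reliably, so the result should be presented as an estimate with its interval, and a non-significant result should not be read as absence of effect.
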